| Lipid panel             | X                      |                       |                                             | T  |                 |                 | T/C  |      | T/C   |      | T    |      | T/C   |                          |              |
| Urinalysis              | X                      |                       |                                             | T  |                 |                 | T/C  |      | T/C   |      | T    |      | T/C   |                          |              |
| Vaccination titer optional           |                        |                       |                                             |    |                 |                 |      |      | T/C   |      |      |      | T/C   |                          |              |
| RNA optional                         | X                      |                       |                                             |    |                 |                 |      |      |       |      |      |      | T/C   |                          |              |
| DNA optional                         | X                      |                       |                                             |    |                 |                 |      |      |       |      |      |      | T/C   |                          |              |
| Safety assessments            |                        |                       |                                             |    |                 |                 |      |      |       |      |      |      |       |                          |              |
| Adverse events          | X                      | X                     | T                                           | T  | T               | T/C             | T/C  | T/C  | T/C   | T/C  | T/C  | T/C  | T/C   | T/C                      |              |
| Individual risk-benefit evaluations  |                        |                       |                                             |    |                 |                 | T    |      | T     |      | T    |      |       |                          |              |
| Sirolimus PK sampling                |                        |                       | T                                           | T  | T               | T               | T    | T    | T     | T    | T    | T    | T     |                          |              |

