### 3. Clinical Trial Design

#### 3.1 Overall Trial Design

The clinical trial is planned as a two-armed, randomized, observer-blind, controlled phase IIb clinical trial for children <4 months of age at inclusion.

The treatment group will receive daily oral mTOR inhibitor (sirolimus) therapy in addition to standard of care (SOC), starting within the first 4 months of life. Sirolimus will be continued until the 2nd birthday when neuropsychologic testing will be done. The control group will receive SOC treatment only. Patients randomized to the treatment group will be followed closely with mandatory study visits at screening, start of treatment (V1), titration visits V2-V4 and at an age of 3, 6, 9, 12, 15, 18, 21 and 24 months for safety measures, to adjust sirolimus dosages following PK testing according to prespecified algorithms and to ensure compliance. In case neonates receive their first dose of IMP under the age of 4 weeks (corrected gestational age <4 weeks of life), caregivers will have up to two additional telephone calls by the study personnel up to the end of the 4th week of life. These calls will take place in those weeks where no titration visit takes place. An end-of-trial visit at 25 months of age will monitor safety parameters after end of trial. Subjects randomized to the control group will be treated according to SOC. No placebo will be administered to reduce the number of laboratory examinations at screening, 6 months, 12 months, and 24 months of age to the minimum required to control for laboratory abnormalities unrelated to the study intervention. Mandatory study visits for the control group are at screening and at 3, 6, 9, 12, 15, 18, 21 and 24 months of age. The enrolment in the primary study ends with the end-of-trial visit at age 25 months. Therapy of TSC manifestations according to SOC in both groups will not be affected by the trial. Seizure diaries, use of anti-seizure medications and concomitant medications, adverse events, vital signs (blood pressure, temperature, heart rate), height, body weight, OFC, and physical / neurological exam, and developmental milestones will be assessed at every visit. EEG and abdominal sonography will be done as described in chapter 6. Neuropsychologic testing will be performed at 12 and 24 months of age.

A schematic of the trial design is shown:

Figure 3: Schematic diagram of trial

[figure not shown]

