Sirolimus will be dispensed by study center personnel on an outpatient basis at start of treatment visit (V1), if necessary, on titration visits (V2-V4) and at each study visit in a three-months interval at 3, 6, 9, 12, 15, 18, and 21 months of age. Caregivers will be provided with an adequate supply for self-administration at home, with exception of the days when PK sampling will be performed, and sirolimus will be administered at the site after blood sample collection. Caregivers will be instructed by the trained study personnel to administer sirolimus exactly as prescribed. The first dose will be administered at the trial center. All dosages prescribed and all dose changes during the study will be recorded on the Dosage Administration Record in the eCRF. The medication administered, specifics of administration, AEs, and comedications are entered into the patient diary by the caregivers. Sirolimus oral solution will be administered in an oral syringe before feeding or meal. Rapamune® oral solution is not allowed to be diluted with grapefruit juice or any other liquids. Caregivers will administer the predetermined amount of clinical trial medication twice daily: in the morning directly before breakfast (e.g. breastfeeding or other food/liquid intake) and in the evening directly before dinner (e.g. breastfeeding or another food/liquid intake). The dosing regimen will differentiate between the two age groups of neonates <4 weeks and infants ≥4 weeks in order to address the reduced metabolism capacity of IMP excipients in the first month of life (see also section “5.2.2.7 Excipients with known effect”). For neonates <4 weeks, the IMP application twice daily will be maintained even for single volumes <0.1 ml. A possibly reduced dosing accuracy for these small volumes will therefore be tolerated in this age group to avoid toxic peak concentrations of IMP excipients. For infants ≥4 weeks receiving a daily dose of <0.2 ml, administration is reduced to once daily in the morning. For infants ≥4 weeks receiving daily volumes <0.1 ml in the morning the administration will be every two days with the double daily dose to ensure dosing accuracy. The application regimen will be switched to a twice-daily regimen by the study team at the earliest timepoint possible. A new oral syringe should be used for each administration. Caregivers will be instructed to ensure the entire dose is administered. In the event of spitting out the study medication without any portion having already been swallowed, the full dose should be re-administered. This should not be done more than once. In case of vomiting, no attempt should be made to replace the vomited dose. If the administration of the medication is missed, it can be carried out up to the next scheduled administration, in concordance with the SmPC. Missed doses should be documented and discussed with the study team at the next visit to work out solutions. On the days of PK sampling, patients should not be administered the sirolimus morning dose until after blood work is drawn so that an accurate trough level can be obtained. On days of scheduled visits, patients should bring their daily dose of sirolimus into the clinic for administration after blood work is drawn. Sirolimus 12h-trough levels will be measured when IMP is administered twice daily, 24h-trough levels in cases of 24h or 48h intervals of administration, at every study visit. Dose adjustments to achieve target levels of 5-10 ng/ml will be made. Trough levels will be communicated to caregivers in person or by telephone by study personnel. Until adjustments are communicated, the current dose will be continued.

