### 5.5.5 Subject Compliance

Compliance is measured by the amount of study medication left in the medication bottles at each study visit.

Subject compliance will be assessed at each visit during the trial and will be verified by interviewing caregivers and through accounting of returned trial medication at each visit and the patient diary kept by the caregiver(s). Compliance will be recorded by measuring the amount of sirolimus returned at each study visit. The person responsible for the clinical trial medication calculates the amount of used medication by subtracting the unused clinical trial medication (in ml) from the total contents of the study medication bottles and comparing it with the documentation of administered medication. The amount of the unused medication and the documentation should be reliable and consistent (with a tolerance of 15%). Details will be recorded in the eCRF.

Inadequately low levels (under the detection level of the laboratory) given the administered dose and not otherwise explicable, e.g. by interindividual rates of metabolization, should raise the suspicion for reduced compliance

Non-compliance (i.e., missed or incorrect dosing) will be documented in the source data and the eCRF. In subjects and / or caregiver(s) of the subject who demonstrate non-compliance between visit intervals, the caregiver(s) of the subject will be counselled by trial staff to address reasons for non-compliance. If after counselling the subject and / or caregiver(s) of the subject continues to exhibit non-compliance over two consecutive trial visits, the subject should be withdrawn from the trial. Dosing interruptions of 7 days or more must be discussed with the sponsor.

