## 6.2 Screening Visit

During the screening visit (screening and/or V1, week 0) eligibility criteria will be assessed, and an informed consent form (ICF) has to be signed prior to study related procedures. A careful history of the patient's illness, including TSC diagnosis, prior anti-TSC therapy, seizure history and prior ASM use will be assessed. A physical and neurological examination, including assessment of anthropometric data and vital signs, will be taken by an experienced team of trained pediatric neurologists, nurses and physiotherapists. Initial laboratory examinations (hematology, chemistry, lipids, urinalysis) and a screening EEG will be conducted. Patients will then be randomized. In case randomization to the treatment group occurs, caregivers will be instructed on how to administer the study medication and will further be advised to seek immediate medical attention on signs of pneumonia (respiratory distress), recurrent infection or appearance of oral aphthosis, as well as to avoid interacting CYP3A4 inhibitors and inducers. In both study arms, caregivers will receive a seizure diary and will be instructed on how to recognize and count possible prospective seizures and how to complete a daily seizure diary.

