Seizure diary: A paper seizure diary for the recording of epileptic seizures will be given to the caregivers at the time of inclusion into the study and will be collected at each study visit and replaced by a new seizure diary. Seizure events recorded by the caregivers will be transferred to the eCRF by study personnel. Documentation for each new seizure diary: seizures [yes/no], if yes: frequency of seizures [weekly = 1, daily = 2, more than daily = 3], type(s) of seizure(s) [Focal motor onset (e.g. automatism, atonic, clonic, hyperkinetic, myoclonic, tonic), Focal nonmotor onset (e.g. autonomic, behaviour arrest, cognitive, emotional, sensory), Focal to bilateral (tonic-clonic), Generalized onset motor (e.g. tonic-clonic, clonic, tonic, myoclonic, myoclonic-tonic-clonic,

|                                                                    |                                              |                                |
|--------------------------------------------------------------------|----------------------------------------------|--------------------------------|
| Clinical Trial Code: PROTECT
EU trial number: 2022-502332-39-00 | Trial Protocol
(Version 06; (01.10.2024)) | Page 74 of 110
CONFIDENTIAL |
|--------------------------------------------------------------------|----------------------------------------------|--------------------------------|

myoclonic-atonic, atonic), Generalized onset non-motor (absence, typical or atypical), Unknown onset motor (tonic-clonic), Unknown onset non-motor (behaviour arrest), Infantile spasms], status epilepticus [n], occurrence and duration of worst episode [no status epilepticus = 0, status lasting half hour to 1h = 2, status lasting 1 h or more = 3], response to treatment in last 3 months [complete cessation of seizures = 1, partial cessation of seizures = 2, no improvement in seizures = 3]. At the time of study inclusion, caregivers will be instructed in the use of the seizure diary and informed about different seizure types, including infantile spasms.

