## 8.6 Period of Observation and Documentation

### 8.6.1 Adverse Events (AEs)

**AEs** will be ascertained by the investigators using non-leading questions, noted as spontaneously reported by the caregiver(s) of the subjects to the medical staff at any time during the trial or observed at any of the clinical trial visit.

The observational period begins with the signature of the informed consent form (ICF) and ends with the end of trial visit (V13). Same applies for SAEs/AESIs. AEs will be interrogated for at each contact between the responsible investigator and the caregiver(s) of the clinical trial subject. Thereafter, the investigator does not need to actively monitor subjects for adverse events. However, if the investigator becomes aware of a serious adverse event with a suspected causal relationship to the IMP (SAR) that occurred after the end of the observational period he or she shall report the SAE without undue delay to the Sponsor, as long as the clinical trial is still ongoing. This kind of SARs is also to be documented in the eCRF.

AEs will be documented in the subject file and in the eCRF. AEs will be reported with patient number, start and end date, description, grading, seriousness, relationship, action taken and outcome. These are the parameters that can be found on the standard AE-eCRF page. If applicable, all medical diagnoses or symptoms occurring prior to the beginning of the period of observation and documentation will be recorded in the eCRF as medical history.

The following general rules apply to the documentation of the AEs and SAEs: The start date of a SAE must not be earlier than that of the corresponding AE. The end date of a SAE is typically the same as that of the AE. The end date of the SAE must not be later than the end date of the corresponding AE. AEs and SAEs that are ongoing at the time of death are considered not resolved or resolving.

All SAEs/AESIs and their relevance for the benefit-risk assessment of the clinical trial will be evaluated continuously during the clinical trial and for the final report. All SAEs/AESIs will be documented in the eCRF and in the 'SAE/AESI Report Form' (see section 8.7.1).

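### As written, the only caregiver diary for adverse events belongs to the sirolimus instructions, so non-serious events may be under-recorded in controls

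*Protocol*

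**What the plan says.** Section 5.4 (Administration) deals with dispensing, syringes, dosing times and missed doses. Among those instructions it states: "The medication administered, specifics of administration, AEs, and comedications are entered into the patient diary by the caregivers". The sentence names no arm, but the first two items it lists exist only for a child receiving sirolimus, because there is no placebo. The patient diary is mentioned once more, in section 5.5.5, beside the returned-medication count as a check on compliance.

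Where the protocol means both arms, it says so. Section 6.2: "In both study arms, caregivers will receive a seizure diary". Section 6.8 describes that diary: "A paper seizure diary for the recording of epileptic seizures will be given to the caregivers at the time of inclusion into the study". Its listed fields cover seizures, status epilepticus and treatment response. They do not cover adverse events or comedications. It is also the only diary in Table 1.

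Section 8.6.1 sets out how adverse events are found, without distinguishing the arms: non-leading questions at each contact between investigator and caregiver, spontaneous reports at any time, and observation at visits. It does not name any diary as a source.

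Section 2.2.1 lists adverse events, SAEs and AESIs as secondary objective 9, to be compared between the groups. Section 9.5.1 tabulates event counts and the number and percentage of children with at least one event.

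**The concern.** A site that follows the text literally would give sirolimus families a document in which to note adverse events and comedications as they occur, and would give control families only a seizure diary. Section 5.1.2 confirms that neither families nor trial staff are blinded.

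Minor, short-lived events (a mild infection, a mouth ulcer, a few days of diarrhoea) are the ones most easily forgotten by the next contact. If they are written down in one arm and recalled from memory in the other, the control column would understate them and the between-arm difference would be tilted against sirolimus. The same applies to comedications. Section 1.3.8 describes information on long-term tolerability in this age group as limited, so this comparison is one that readers will look for. No later analysis can recover an event that was never recorded.

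**Working it through.** The protocol gives no recall or capture figure, so there is no plan figure to reproduce. The check sets the sections side by side, counts the scheduled assessments, and adds an illustration.

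**1. Which arm has a written adverse event record?**
- Patient diary (adverse events, comedications, doses): 5.4 and 5.5.5, both about sirolimus.
- Seizure diary (seizures only): 6.2, 6.8 and Table 1, stated for both arms.
- Adverse event diary for controls: not described anywhere.
- Sentence excluding controls from the patient diary: none.

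**2. Scheduled adverse event assessments after V1 (Table 1).**
- Sirolimus: V2 to V13 = 12. V4 and V5 may be omitted under stated conditions.
- Control: V5 to V13 = 9, since V2-V4 are marked for the treatment group only. V5 carries the same conditional footnote.
- Section 3.1 agrees on spacing: "Mandatory study visits for the control group are at screening and at 3, 6, 9, 12, 15, 18, 21 and 24 months of age". The end-of-trial visit at 25 months completes the nine.

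Sirolimus families also have calls in the first weeks if dosing starts before 4 weeks of age, a call about 7 days after a dose is doubled (Table 5), and repeat trough-level appointments after dose adjustments.

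**3. What applies to both arms?** Section 1.3.1 gives standard-of-care evaluations every 4-6 weeks in the first year and every 8-12 weeks in the second. Section 6 says data from these visits are entered in the eCRF. With questioning at each contact under 8.6.1, the recall interval for a control family can be well below three months. These channels serve sirolimus families equally, so they shorten recall in both arms and leave the extra written prompt in one.

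**4. Illustration (assumptions, not protocol figures).** Let m be the mean number of true events per child, equal in both arms, and c the share recorded. With Poisson counts, the proportion of children with at least one recorded event is P = 1 - exp(-m × c), and the expected recorded events per 30 children are 30 × m × c. Take c = 0.9 for sirolimus and 0.8 or 0.6 for controls.

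| m | Sirolimus P (c = 0.9) | Control P (c = 0.8) | Control P (c = 0.6) | Spurious difference, points |
|---|---|---|---|---|
| 0.7 | 1 - exp(-0.63) = 47% | 1 - exp(-0.56) = 43% | 1 - exp(-0.42) = 34% | 3.9 to 12.4 |
| 1.5 | 1 - exp(-1.35) = 74% | 1 - exp(-1.20) = 70% | 1 - exp(-0.90) = 59% | 4.2 to 14.7 |

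At m = 1.5 the event counts per 30 children are 30 × 1.5 × 0.9 = 40.5 on sirolimus, against 36.0 (c = 0.8) or 27.0 (c = 0.6) in controls. With c = 0.9 in both arms the spurious difference is 0 at every m. The direction follows from the asymmetry; the size follows only from the assumed c and m.

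**The case against.** The case on the other side has real weight.

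- *No sentence restricts the diary to sirolimus families.* True. The restriction is inferred from where the sentence sits, what the diary contains and how 5.5.5 uses it. If the sponsor intends both arms to keep it, the text still needs correcting, because a site reading 5.4, 5.5.5 and 6.2 would not hand it to controls.
- *Section 8.6.1 treats the arms alike and does not list the diary.* Also true. Section 6.8 says seizure diary entries are transferred to the eCRF; no such step is stated for adverse events in the patient diary. The diary may act only as a prompt. It is nevertheless examined for compliance at each visit under 5.5.5, so what families wrote there is in front of staff.
- *Many events are covered in both arms.* Infection or unexplained rash leading to an unplanned consultation is an AESI (8.1.4), with 24-hour reporting. Serious and hospitalised events are hard to miss. Section 6.8 has caregivers asked about medication at every visit. This narrows the point to non-serious clinical events and to the completeness of comedication records.
- *No test of adverse events is planned.* Correct: 9.5.1 is descriptive, so no formal error rate is at stake.

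A reader might infer that control families must recall up to three months of events, or that sirolimus rates are inflated. The documents do not support either. Spontaneous reports are accepted at any time and other contacts fall between the mandatory visits. A diary makes the sirolimus record more complete rather than false; the possible shortfall is in the control column.

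**Conclusion.** The point holds in limited form and should be corrected. The protocol describes a caregiver record of adverse events and comedications only within sirolimus handling, and gives both arms only a seizure diary. On the best-supported reading, non-serious clinical adverse events and comedications may be under-recorded in controls, which would bias the descriptive between-arm comparison against sirolimus.

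The size cannot be computed from the documents. The 4 to 15 points above rest wholly on assumed capture rates and event frequencies and should not be cited as an estimate. The columns also do not map exactly onto diary use: under the as-treated rule in 9.1, sirolimus children lost before 6 months count as standard of care. The primary endpoint is not affected.

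**What to change.** - In 5.4, 6.2 and 6.8, give caregivers in both arms the same adverse event and comedication page, for example within the seizure diary both already receive. Keep the dosing page for the sirolimus arm only.
- Review that page with the same questions in both arms at the common visits V5-V13.
- Name the page in 8.6.1 as a source of adverse events.

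The cost is a short amendment, slightly more writing for control caregivers and some more adverse event entry at sites. It needs no extra visit or staff. It does not remove the additional treatment-group contacts (V2-V4, calls, trough-level appointments), so tabulating events from V5-V13 separately would be a useful complement. Section 3.2 places last subject last visit in Q2 2029 and this protocol version is dated October 2024, so much of the data can still be collected on equal terms.

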| Interventions and Treatments | 
Investigational Medicinal Product (IMP): mTOR inhibitor sirolimus
Trade name: Rapamune®
 
Pal formulation: 1 mg/ml oral solution
Routes of administration: oral
 
Dosage: Sirolimus will be administered as oral solution adapted to body surface area with a starting dose of 0.5 mg/m^2/day (<1 months of age) to 0.9 mg/m^2/day (3- <4 months of age) divided BID (twice daily) until 2 years of age. Sirolimus 12h trough levels will be measured at every study visit and doses titrated and adapted to reach target trough levels of 5-10 ng/ml.
 
Control intervention: standard of care (SOC)
 
Treatment duration: starting within the first 4 months of life and continued until the 2nd birthday.
 |
| Ethical Considerations       | 
Reducing neuropsychologic deficits will improve quality of life and participation, as well as reduce morbidity and mortality, hospitalization, socio-economic costs, and the number of pharmacologic and non-pharmacologic therapies required for the treatment of associated long-term complications.
                                                                                                                                                                                                                                                                                                                                                                                                                                                                        |
| Number of Sites              | 17-20                                                                                                                                                                                                                                                                                                                                                                                                                                                                                                                                                                                                                                                                                                                                                                                |

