|--------------------------------------------------------------------|----------------------------------------------|--------------------------------|
| Clinical Trial Code: PROTECT
EU trial number: 2022-502332-39-00 | Trial Protocol
(Version 06; (01.10.2024)) | Page 59 of 110
CONFIDENTIAL |
|--------------------------------------------------------------------|----------------------------------------------|--------------------------------|

regimen, which was shown to reduce absolute doses [89, 90]. To reduce the occurrence of AEs we will target trough levels of 5-10 ng/ml.

Table 4: Starting daily dose of IMP

| Age group (months) | Daily Dose (mg/m  /day) |
|--------------------|-------------------------------------|
| 0 - <1             | 0.5                                 |
| 1 - <2             | 0.6                                 |
| 2 - <3             | 0.74                                |
| 3 - <4             | 0.9                                 |

In general, the daily dose is divided into two administrations. In particular, a distinct dosing regimen will be used for neonates <4 weeks addressing the reduced excipient metabolism (see also sections “5.2.2.7 Excipients with known effect” and “5.4 Administration”): For neonates <4 weeks, the BID regimen will be maintained for daily volumes <0.2 ml, even for single volumes <0.1 ml. For infants ≥4 weeks receiving a daily dose <0.2 ml, administration is reduced to once daily in the morning to ensure dosing accuracy and switched to a BID regimen by the study team at the earliest timepoint possible. For infants ≥4 weeks receiving daily volumes <0.1 ml in the morning the administration will be every two days with the double daily dose to ensure dosing accuracy. Subjects randomized to the treatment group will receive oral sirolimus (Rapamune® oral solution) therapy. Sirolimus will be administered adapted to body surface area (BSA) with an age-dependent starting dose of **0.5 mg/m^2/day (0 - <1 months of age) to 0.9 mg/m^2/day (3 - <4 months of age)** divided BID, in addition to SOC.

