#### Pharmacokinetics

During the titration period, pre-dose PK blood samples will be collected immediately prior to dosing on the study day. Any sample collected outside of these parameters is not considered a true trough and therefore should not be used as a basis for adjusting the patient's dose. It is expected that all patients will achieve the desired target pre-dose trough level ( $C_{min}$ ) during the titration period (V1-V4). A local lab (at the treating centre) will measure the sirolimus concentrations. HPLC-MS/MS is the most appropriate method, other techniques (e.g. immunoassays) tend to under-/overestimating of drug concentrations. After obtaining current trough levels, the site will adjust the future dose as described in section 5.5.3 (to maintain, increase or decrease the dose). In order to minimize total blood samples, the amount of blood required for sirolimus PK samples will be 0.5 mL.

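### For 48-hour dosing, section 5.4 adjusts the dose on a mid-interval 24-hour level, while sections 6.5 and 6.8 adjust on pre-dose samples, so Table 5 can give the same child two different actions

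*Protocol*

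**What the plan says.** Sections 5.4 and 5.5 of the Protocol set up the regimen: "For infants ≥4 weeks receiving daily volumes <0.1 ml in the morning the administration will be every two days with the double daily dose". For sampling, section 5.4 takes 12-hour levels under twice-daily dosing and "24h-trough levels in cases of 24h or 48h intervals of administration, at every study visit", and continues: "Dose adjustments to achieve target levels of 5-10 ng/ml will be made".

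The same section says that on PK days "patients should not be administered the sirolimus morning dose until after blood work is drawn so that an accurate trough level can be obtained". It also has sirolimus given at the site after the draw.

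Section 6.8 (Pharmacokinetics), in a paragraph that opens with the titration period, says that "pre-dose PK blood samples will be collected immediately prior to dosing on the study day". It adds: "Any sample collected outside of these parameters is not considered a true trough and therefore should not be used as a basis for adjusting" the dose. Section 6.5 covers the treatment visits. It bases adjustment on pre-dose concentrations and states the 5-10 ng/ml target as Cmin.

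Table 5 (section 5.5.3) turns a level into an action. Below 5 ng/ml all later doses are doubled, and from 5 to 10 nothing changes. Above 10 and up to 15 nothing changes unless there is a clinically significant event or laboratory abnormality. Above 15 and up to 20 doses go to 75%; above 20 one dose is skipped and later doses go to 50%. The table does not distinguish dosing intervals or sampling times.

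**The concern.** Under twice-daily dosing a 12-hour level is the pre-dose level, and under once-daily dosing so is a 24-hour level. Sections 5.4, 6.5 and 6.8 agree for both. They part company only for 48-hour dosing, where the 24-hour sample falls halfway through the interval.

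A site that follows section 5.4 adjusts on a sample that section 6.8, by its own definition, says should not guide dosing. A site that follows sections 6.5 and 6.8 draws at 48 hours and departs from section 5.4. Whichever level is drawn, it enters the same Table 5 bands. At stake is consistent handling of a drug that section 5.5 describes as having a narrow therapeutic window, in very small infants and in those whose volume has just been cut under Table 5 or Table 6.

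**Working it through.** **1. Can a site comply with everything?** Take a child dosed on the mornings of day 0 and day 2.

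- Section 5.4, sampling rule: draw on the morning of day 1 (24 h). No dose is due.
- Section 5.4, PK-day rule: hold the morning dose until after the draw, then give it at the site. On day 1 there is no dose to hold or give.
- Sections 6.8 and 6.5: draw immediately before a dose, which means the morning of day 2 (48 h).

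Drawing on day 1 breaks the pre-dose rule, drawing on day 2 breaks the 24-hour rule, and dosing on day 1 breaks the 48-hour schedule. No passage exempts the 48-hour regimen from sections 6.5, 6.8 or Table 5.

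**2. How far apart are the two levels?** The only half-life in the Protocol (section 5.2.2.5) is 62 ± 16 h, in renal transplant patients receiving ciclosporin. No infant value is given. With first-order decline, C24/C48 = 2^(24/t½).

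| t½ | C24/C48 | Pre-dose level when the 24 h level reads 5 | 24 h reading when the pre-dose level is 5 |
|---|---|---|---|
| 78 h | 1.24 | 4.0 | 6.2 |
| 62 h | 1.31 | 3.8 | 6.5 |
| 46 h | 1.44 | 3.5 | 7.2 |
| 24 h (assumed) | 2.0 | 2.5 | 10.0 |

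The direction holds at any half-life. The size in infants cannot be fixed from the document.

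**3. Effect on Table 5.** At 62 h, a pre-dose trough between 5/1.31 = 3.8 and 5.0 ng/ml gives a 24-hour reading between 5.0 and 6.5. The 24-hour level leads to no adjustment; the pre-dose level leads to doubling. The upper cut-offs shift in the same way: a pre-dose level of 15/1.31 = 11.5 reads as 15, and 20/1.31 = 15.3 reads as 20.

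**4. Is average exposure misjudged?** Steady state, one compartment, instant absorption, one unit of drug per day, k = ln 2/62 = 0.01118 per hour:

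- 24 h level under 48-hour dosing: 2e^(−24k)/(1 − e^(−48k)) = 3.68
- 48 h pre-dose level: 2e^(−48k)/(1 − e^(−48k)) = 2.82
- 12 h trough under twice-daily dosing: 0.5e^(−12k)/(1 − e^(−12k)) = 3.48
- average concentration: 1/(24k) = 3.73

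The 24-hour level is therefore 3.68/3.73 = 0.99 of the average and 3.68/3.48 = 1.06 times the twice-daily trough. The 48-hour pre-dose level is 2.82/3.48 = 0.81 of the twice-daily trough. Average exposure is not overstated; only Cmin is.

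**5. Can the regimen occur?** This uses the Protocol's body-surface formula (section 5.5), the 1 mg/ml strength and assumed body sizes.

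- 46 cm, 2.5 kg: 0.190 m² × 0.5 mg/m²/day = 0.095 ml/day. A child started as a neonate and still on this volume falls under the 48-hour rule from 4 weeks. Started instead at the 1 to <2 month dose, the same child gets 0.190 × 0.6 = 0.114 ml/day and does not.
- 54 cm, 4.2 kg: 0.265 m² × 0.6 = 0.159 ml/day, and 0.080 ml after a 50% reduction.

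**The case against.** Section 5.4 is the only place that names a sampling time for 48-hour dosing, so it can be read as a deliberate exception to a general rule. Section 6.8 does not mention 24-hour or 48-hour intervals, and its paragraph is worded for titration. In the model above, the 24-hour level also lies closer than the 48-hour pre-dose level to the trough a child on twice-daily dosing would have. This last point stands, and it is why the review does not say which sampling time to adopt. The exception reading is weaker. The Protocol nowhere declares an exception, section 6.5 carries the pre-dose rule and the Cmin target beyond titration, and section 5.4 conflicts with its own instruction to dose after the draw.

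The reach is also small. Section 5.4 requires a switch to twice-daily dosing as early as possible, and the treated arm has 30 children. That stands.

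Four stronger readings might be inferred, and the document does not support them:

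- **Exposure is overstated.** Step 4 of the working shows that average concentration is not.
- **Reported results are biased.** No primary or secondary endpoint uses Cmin or target attainment, and section 9 plans no such table.
- **The synopsis is a further contradiction.** It says "Sirolimus 12h trough levels will be measured at every study visit", but it is describing the standard twice-daily regimen, for which section 5.4 says the same.
- **The eCRF lacks the time since last dose.** The PK page is not shown, and section 5.4 already has caregivers record details of administration in the diary.

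**Conclusion.** The contradiction is real, but narrow. For infants of at least 4 weeks on 48-hour dosing, sections 5.4, 6.5 and 6.8 cannot all be followed, and Table 5 can prescribe different actions for the same child depending on which is used. At the document's 62 ± 16 h half-life, the 24-hour level exceeds the pre-dose level by about 31% (24-44%). At 62 h, pre-dose troughs of about 3.8-5.0 ng/ml would read as in target.

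These figures assume first-order decline and a half-life that does not come from infants. They describe nominal Cmin. Few children are likely to be affected, often temporarily, and the primary analysis is untouched. The passages still need to be reconciled, because they decide a dosing action in very small infants.

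**What to change.** Reconcile sections 5.4, 6.5 and 6.8 so that one sampling rule applies to 48-hour dosing, including what happens to dosing on the day of the draw. State in Table 5 which kind of level its bands are read on. Which rule to adopt is the sponsor's decision. Record the time since last dose with each PK level, if the eCRF does not already capture it.

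The cost is a few sentences of Protocol wording, a note to Table 5 and at most one eCRF field. Depending on the rule chosen, a visit may have to be planned around the child's dosing day.
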